### 2.9. Data Management and Document Conservation

The researchers should document the data into the case report form (CRF) timely, completely, correctly, and clearly according to original data. The clinical supervisor will confirm that all the CRFs are filled correctly and completely and consistent with the original data. The errors and omissions must correct them in time, the original records should be kept clear and visible when modifying, and the correction should be signed and dated by the researcher. After checked and signed by the supervisor, the CRFs will be sent to the trial data administrator. The data administrator will check the data again before data entry. If any problem is found, they will notify the supervisor and ask the researcher to respond. The exchange between them should be kept in the form of a query table. The data administrator also should understand the content and coding of each item before data entry. The data entry personnel should input the data twice. After data entry, the quality and *l* logicality will be checked. The documents will be requested to conserve by every unit after the study. Researchers should preserve the documents of the clinical trial for five years.

### 2.10. Sample Size Calculation

According to previously published research [11], the annual conversion rate of IGT into T2DM was 1.5% in the TCM group and 10% in the control group. We predicted that the annual conversion rate of IGT into T2DM was 5.7% in the TCM comprehensive intervention group. Therefore, assuming that *α* = 0.05 and *β* = 0.1 according to the one-sided test, u*α* = 1.645 and u*β* = 1.282, and the data will be placed in the formula to obtain *n* = 299.94. Therefore, each group needs more than 300 participants, for a total of 600 participants.

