## 2. Methods

### 2.1. Trial Design

This study is a multicenter cohort study with two arms. A total of 600 participants will be recruited. The participants will be divided into either intervention or control groups according to their own desire, and the exposure factor is the application of TCPMs. All participants will be encouraged to lead a healthy lifestyle, and the intervention group also used TCPMs based on syndrome differentiation. Incident diabetes and normalization of blood glucose are indexes of end point. Safety assessments and adverse event monitoring will also be conducted. The treatment duration is set for 24 weeks, and we will follow-up for another 2 years.

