### 2.5. Interventions

The participants will be divided into either the intervention group or the control group (1 : 1). The control groups will conduct lifestyle intervention alone, and the intervention group will use TCPMs on the basis of lifestyle intervention.

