### 2.7. Study Visits and Data Collection

The study is divided into two periods, a 24-week drug intervention period and a 24-month follow-up period. After the intervention period commences, telephone visits will take place every 2 weeks and outpatient visits every 4 weeks. When the follow-up period commences, outpatient visits will take place every 6 months. An overview of data capture can be found listed in Table 1.

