### 2.11. Statistical Analysis

Three datasets will be used for statistical analysis, including a full-analysis set (FAS), per-protocol analysis set (PPS), and safety analysis set (SS). The FAS is the dataset composed of participants who have at least one postmedication evaluation data. The last observation carried forward (LOCF) method will be used for the missing data supplement. The PPS is the dataset composed of participants who meet the inclusion criteria, show good compliance, and complete the treatment plan. The SS is the dataset of all participants randomized to study, and safety record will be assessed, including adverse events and laboratory test results. All statistical tests are two-sided tests, and *P* < 0.05 will be considered statistically significant. Enumeration data will be expressed as frequency and analyzed using the chi-square test or Wilcoxon rank sum test. Measurement data will be described by means, standard deviation, maximum value, and minimum value and compared between groups using the group *t*-test, Fisher's exact test, or Wilcoxon rank sum test. Statistical analysis will be completed by the third-party statisticians.

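### The 90% power in section 2.10 does not follow from its annual rates, and about 300 per group is approached only over roughly two years or more, mostly after the 24-week drug period, with no stated horizon or post-treatment assumption

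*Protocol article*

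**What the plan says.** Section 2.10 of the protocol article cites published research in which "the annual conversion rate of IGT into T2DM was 1.5% in the TCM group and 10% in the control group". It then sets its own figure for the intervention group: "We predicted that the annual conversion rate of IGT into T2DM was 5.7% in the TCM comprehensive intervention group". The calculation is made "assuming that *α* = 0.05 and *β* = 0.1 according to the one-sided test", with normal quantiles 1.645 and 1.282. It gives n = 299.94, from which the article concludes that "each group needs more than 300 participants, for a total of 600 participants".

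Section 2.1 describes the exposure: "The treatment duration is set for 24 weeks, and we will follow-up for another 2 years". Section 2.7 repeats this: "The study is divided into two periods, a 24-week drug intervention period and a 24-month follow-up period". Table 1 ends the drug period at week 24 and has visits at 12, 18, 24 and 30 months.

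Section 2.11 states: "All statistical tests are two-sided tests, and *P* < 0.05 will be considered statistically significant".

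The article does not say over what period conversion is compared for the sample size, how 5.7% was reached, or what rate is expected once scheduled drug ends.

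**The concern.** An annual rate becomes a sample size only through a time horizon. Here the horizon matters twice. It fixes the cumulative risks that enter the formula. It also fixes how much of the observed time lies beyond the 24 weeks of scheduled drug: 28 of 52 weeks in the first year, about 77% of two years, and about 82% of 30 months. A longer horizon yields more events, but it also leans harder on an effect that continues after treatment.

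At stake is the stated 90% power. If it rests on an unstated horizon and an unstated carry-over, readers cannot tell whether a null conversion result is informative, and the study may be much weaker on incident diabetes than section 2.10 suggests.

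**Working it through.** **Inputs.** Annual rates 10% and 5.7%, quantiles 1.645 and 1.282, and 300 per group (section 2.10); two-sided 0.05, so 1.96 (section 2.11); drug for 24 weeks (sections 2.1 and 2.7); last visit at 30 months (Table 1).

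**Step 1: reproduce n at one year.** With n = (z_α + z_β)² [p₁(1−p₁) + p₂(1−p₂)] / (p₁−p₂)²:

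- (1.645 + 1.282)² = 8.567
- p₁(1−p₁) + p₂(1−p₂) = 0.0900 + 0.05375 = 0.14375
- (0.10 − 0.057)² = 0.001849
- n = 8.567 × 0.14375 / 0.001849 = 666 per group

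The pooled-variance formula gives 669, or 714 with continuity correction. A two-sided test needs about 817 to 821. None is near 299.94.

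**Step 2: power of 300 per group at one year.** Power = Φ(|p₁−p₂| / √{[p₁(1−p₁) + p₂(1−p₂)]/300} − z_α).

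- Standard error = √(0.14375/300) = 0.02189; ratio = 0.043/0.02189 = 1.964
- One-sided: Φ(1.964 − 1.645) = 62.5% (62.3% with pooled variance)
- Two-sided: Φ(1.964 − 1.96) = 50%

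This already grants 5.7% for the whole year, including the 28 weeks without scheduled drug.

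**Step 3: what horizon gives about 300?** Doubling the rates by simple addition gives 20% against 11.4%: 8.567 × (0.1600 + 0.1010) / 0.086² = 302 per group (305 with pooled variance, 301 by arcsine). Compounded over two years (19.0% against 11.1%), n is about 344. Compounded over 30 months (23.2% against 13.6%, carried below unrounded as 13.65%), n is about 280. So 300 fits a horizon of roughly two years or more, although no variant gives exactly 299.94. The article states no such horizon.

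**Step 4: dependence on persistence, at an assumed 30 months.** Assume constant hazards, 300 per group and no dropout.

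- Control hazard: −ln(0.90) = 0.1054 per year. Treated hazard: −ln(0.943) = 0.0587 per year. Midway between them: 0.0820 per year.
- Treated risk = 1 − exp{−[0.0587 × 24/52 + h_off × (2.5 − 24/52)]}. Control risk = 1 − exp(−0.1054 × 2.5) = 23.2%.

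| Effect after week 24 | h_off per year | Treated risk | One-sided power | Two-sided power |
|---|---|---|---|---|
| Full | 0.0587 | 13.6% | 92% | 86% |
| Half the hazard reduction | 0.0820 | 17.7% | 51% | 39% |
| None | 0.1054 | 21.5% | 12% | 7% |

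At one year with no carry-over, the treated risk is 8.0% against 10%, and one-sided power is 21%.

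**The case against.** The strongest reply is that 5.7% may already allow for stopping the drug. It is far above the 1.5% cited for the TCM group. Running 1.5% per year for 24 weeks and 10% per year for the other 28 weeks gives 1 − exp{−(0.0151 × 24/52 + 0.1054 × 28/52)} = 6.2% in year one, close to 5.7% with no carry-over. This stands as far as it goes: one cannot say that the authors treated the drug as acting all year. But the article gives no basis for 5.7%, the reading does not explain 5.7% in a second year with no scheduled drug, and it leaves the one-year n at about 666 to 669.

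Three stronger inferences are tempting, and the document supports none of them:

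- A reader might infer that the 90% is correct provided the effect persists. It is not: at one year, full persistence gives only 62%, and under the planned two-sided test full persistence to 30 months gives 86%. Nor must the effect last the full two years in every calculation. With simple addition of rates over 24 weeks plus two years, about 1.75 years of persistence is enough for 90% one-sided.
- A reader might infer that the plan specifies one pooled 30-month comparison. No section does, and the Discussion says that both short-term and long-term effects are of interest. The 30-month figures are therefore an illustration.
- A reader might infer that participants take no TCPM after week 24. No study drug is scheduled then, but exposure is self-chosen, nothing in the article forbids continued use, and Table 1 records TCPM use through month 30.

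It can also be said that a null conversion result alone would not show lack of effect, because the declared primary outcome is change in FBG, 2h PBG and HbA1c, with glucose measured every 4 weeks on drug. That is right and limits the harm. It does not repair the stated power.

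**Conclusion.** The point holds in this form: the 90% power of section 2.10 does not follow from its own annual inputs, and the horizon and post-treatment effect on which any such figure depends are not stated. At one year the shortfall is a matter of arithmetic: 300 per group against about 666 to 669 needed one-sided, with power of about 62% one-sided or 50% two-sided. Over longer horizons the answer turns on persistence: at 30 months, two-sided power runs from 86% with full persistence through 39% with half to 7% with none.

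The 30-month range rests on the assumed horizon, constant hazards, a control rate of 10% per year, 300 analysed per group and no dropout. It also takes 5.7% per year as the rate during the 24 weeks of drug. The one-year result rests only on the rates, α, β and n that the article gives, with the two-sided figure using the test in section 2.11. Whether 5.7% already includes dilution cannot be settled from the article.

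**What to change.** In section 2.10:

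1. State the horizon at which conversion is compared.
2. State how 5.7% was derived and whether it allows for the end of scheduled drug.
3. Replace the single annual rate with two rates for the TCPM group, one for the 24-week drug period and one for the follow-up, so that the assumed persistence is visible.
4. Replace the unconditional 90% with the power of 300 per group at that horizon under full, partial and no persistence, computed two-sided to agree with section 2.11.

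Optionally, report conversion for weeks 0 to 24 and for week 24 to month 30 separately, using glucose measurements already scheduled in Table 1. This may be left to the analysis plan, and the period estimates would be less precise than the total.

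The cost is some wording and a small table in section 2.10, and a less favourable stated power. No change to treatment or enrolment is proposed.

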We hypothesize that the prediabetic patients will benefit from TCPMs. If successful, this trial may provide comprehensive intervention plans that choose suitable TCPMs for diabetes prevention according to syndrome differentiation. Although clinical trials are strictly designed, there might also be potential limitations. Firstly, there is no placebo in the control group. Secondly, the long treatment and follow-up period may lead to poor patient compliance, which might greatly influence the therapeutic effect. More effort should be made to find a solution in future trials.

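### Section 2.10 enrols exactly the computed 300 per group, so the 90% power for diabetes conversion leaves no room for loss, although the plan withdraws participants and the PPS drops them

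*Protocol article*

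**What the plan says.** All references are to the protocol article.

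- **Section 2.10 (sample size).** The source rates are given as "the annual conversion rate of IGT into T2DM was 1.5% in the TCM group and 10% in the control group". The planning rate for the intervention arm is set separately: "We predicted that the annual conversion rate of IGT into T2DM was 5.7% in the TCM comprehensive intervention group". The test is "according to the one-sided test", with "u*α* = 1.645 and u*β* = 1.282". The result is "the data will be placed in the formula to obtain *n* = 299.94", followed by "Therefore, each group needs more than 300 participants, for a total of 600 participants". No loss rate appears.
- **Section 2.3.** The 600 is the number recruited, split 1:1.
- **Section 2.7 and Table 1.** There are 24 weeks of treatment and then 24 months of follow-up, with the last visit at 30 months.
- **Sections 2.4.5 and 2.4.6.** Participants are suspended or withdrawn for reasons that include poor drug compliance, related adverse reactions, pregnancy, unwillingness to continue, loss of contact, poor efficacy, cost and moving away. Those withdrawn because glucose rises clearly or because of hypoglycaemia are still counted as complete cases, with the effect judged invalid.
- **Section 2.11.** The FAS needs one evaluation after medication and fills gaps by LOCF. For the PPS: "The PPS is the dataset composed of participants who meet the inclusion criteria, show good compliance, and complete the treatment plan". All tests are two-sided.
- **Section 3.** The stated limitations include that "the long treatment and follow-up period may lead to poor patient compliance, which might greatly influence the therapeutic effect".

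**The concern.** A computed requirement is a number of participants who contribute an outcome. Here the same number is used as the number enrolled. The surplus is 300 − 299.94 = 0.06 participants per group, and the sentence that sets it cannot be met as written: two groups each above 300 do not add up to 600. The calculation therefore allows for no loss over 30 months, in a study whose own rules remove participants for many reasons.

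What is at stake is how a non-significant conversion result would be read. It would be set against a 90% that made no provision for the withdrawals the plan itself describes.

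**Working it through.** **1. The plan's own figure.** With 10% vs 5.7%, one-sided α = 0.05 (1.645) and β = 0.1 (1.282), the pooled two-proportion formula is

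n = [1.645·√(2p̄q̄) + 1.282·√(p₁q₁ + p₂q₂)]² / (p₁ − p₂)².

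Here p̄ = 0.0785, √(2p̄q̄) = 0.3804, √(p₁q₁ + p₂q₂) = 0.3791 and p₁ − p₂ = 0.043. This gives 669 per group one-sided, or 821 two-sided (1.96 in place of 1.645). The 299.94 is not reproduced. The nearest route found doubles the annual rates to 20% vs 11.4%, which gives 302 to 307 one-sided depending on the variance form; section 2.10 states no such step. The loss question is therefore examined on more than one basis.

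**2. Completer-type count (PPS), 299.94 taken at face value.** At n = 299.94 the standardised effect is 1.645 + 1.282 = 2.927. With a retained fraction f, equal in both arms, power = Φ(2.927·√(300f/299.94) − 1.645).

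| Loss (assumed) | Evaluable per group | One-sided power |
|---|---|---|
| 0% | 300 | 90.0% |
| 10% | 270 | 87.1% |
| 20% | 240 | 83.5% |
| 30% | 210 | 78.9% |

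**3. Full 30-month horizon.** Compounding the annual rates gives 1 − 0.9^2.5 = 23.2% and 1 − 0.943^2.5 = 13.6%. The pooled formula then needs 283 per group one-sided and 347 two-sided. In the table below, the completer columns use 300(1 − d) per group, where d is the loss.

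The FAS columns keep 300 per group and let LOCF count anyone who drops out unconverted as a non-event. The conversion hazards are λ = −ln 0.9 = 0.1054 and −ln 0.943 = 0.0587 per year. The dropout hazard is γ = −ln(1 − d)/2.5, the same in both arms. The observed conversion proportion is λ/(λ + γ)·[1 − e^(−2.5(λ + γ))]. At d = 20%, γ = 0.0893 and the observed proportions are 20.9% vs 12.3%.

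| Loss (assumed) | Completers, one-sided | Completers, two-sided | FAS with LOCF, one-sided | FAS with LOCF, two-sided |
|---|---|---|---|---|
| 0% | 91.5% | 85.4% | 91.5% | 85.4% |
| 10% | 88.8% | 81.6% | 90.1% | 83.3% |
| 20% | 85.3% | 76.9% | 88.4% | 81.0% |
| 30% | 81.0% | 71.2% | 86.4% | 78.3% |

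**4. One-year horizon, as the annual rates are printed.** With no loss, 300 per group gives 62% one-sided and 50% two-sided. At 240 per group the figures are 54% and 42%.

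On every basis power falls as loss rises. The fall is smaller in the FAS than among completers.

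**The case against.** The strongest reply is that withdrawal is not loss from analysis. The FAS keeps anyone with one evaluation after medication, LOCF fills the gaps, and those withdrawn for rising glucose stay in as complete cases. This stands. A reader might infer that every withdrawal lowers n and that no analysis set can reach the stated power; the documents do not support that. In the FAS the harm comes through conversions that are never observed, and it is the smaller one in step 3.

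Three further points also stand in part.

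- **Complete follow-up is not strictly the condition for 90%.** If conversion is counted over the full 30 months, 300 per group keeps 90% one-sided among completers up to about 4–6% loss (1 − 287/300 with follow-up of 24 weeks plus 24 months; 1 − 283/300 with 2.5 years). On the annual rates as printed, complete follow-up would not deliver 90% at all.
- **The cited text has limits.** PPS membership turns on the 24-week treatment plan, so it is not shown to depend on retention to 30 months. The limitation in section 3 concerns compliance and therapeutic effect. It should not be read as a forecast of attrition.
- **The power figure is narrow.** It concerns conversion only; section 2.6.2 names changes in FBG, 2h PBG and HbA1c as primary.

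One could also say that an article leaves the loss allowance to the full protocol. That does not answer the point, because the article fixes both the computed and the recruited number, and no room is left between them.

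**Conclusion.** The point holds in limited form. Section 2.10 enrols the computed number and reserves nothing for loss, so even at face value its 90% for conversion requires essentially no loss.

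- **PPS or any completer analysis:** about 87%, 83.5% and 79% one-sided at 10%, 20% and 30% loss, taking 299.94 at face value.
- **FAS:** from about 85% two-sided with no loss to 83%, 81% and 78%, with rates compounded to 30 months.

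These sizes rest on loss rates that I assumed, on equal loss in both arms and, for the FAS, on constant hazards, constant dropout unrelated to conversion, and the 30-month horizon.

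It would be tempting to write into the protocol that 20% loss leaves 240 per group and about 83% power. That would be wrong: the figure inherits 299.94, and the printed annual rates at 240 per group give about 54% one-sided and 42% two-sided. This should be put right, but the failure of 299.94 to follow from its inputs and the one-sided sizing against two-sided testing are the larger faults in the same section.

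**What to change.** Keep 600 enrolled. In section 2.10:

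1. State the horizon over which conversion is counted, and the formula.
2. State an expected loss rate to that horizon, an expected rate of exclusion from the PPS, and the evaluable number per group that each leaves.
3. Replace 90% with the power recomputed at those numbers from the stated rates, under the two-sided test of section 2.11, separately for FAS and PPS. Do not start from 299.94. As an illustration, with a 30-month horizon and 20% loss, the figures would be about 81% for the FAS and about 77% at 240 completers per group.
4. Reword the closing sentence so that evaluable and enrolled numbers are given separately and add up.

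The cost is a few sentences and a short recalculation, with no extra participants. The downside is a less favourable stated power, markedly so if a one-year horizon is kept.

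### The 299.94 per group in section 2.10 does not follow from its annual rates (about 658 to 670 needed); the time horizon, cumulative risks and formula must be stated, with the power that 600 participants deliver

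*Protocol article*

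**What the plan says.** Section 2.10 (Sample Size Calculation) cites earlier research in which "the annual conversion rate of IGT into T2DM was 1.5% in the TCM group and 10% in the control group". It then sets the study's own assumption: "We predicted that the annual conversion rate of IGT into T2DM was 5.7% in the TCM comprehensive intervention group". The error rates are given as "assuming that *α* = 0.05 and *β* = 0.1 according to the one-sided test", with normal deviates 1.645 and 1.282. The result is reported as "the data will be placed in the formula to obtain *n* = 299.94", and the section ends: "Therefore, each group needs more than 300 participants, for a total of 600 participants". The formula is not shown. No cumulative risk, time horizon or allowance for loss is given.

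Three other places bear on the figure:

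- Section 2.7: "The study is divided into two periods, a 24-week drug intervention period and a 24-month follow-up period". The last visit in Table 1 is at 30 months.
- Section 2.11 makes all tests two-sided at P < 0.05.
- Section 3 warns that "the long treatment and follow-up period may lead to poor patient compliance".

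**The concern.** All the inputs to the calculation are printed, so the result can be checked, and it fails the check. The only rates given are annual, and annual rates of 10% and 5.7% call for more than twice 299.94 per group. Something was done to the rates that the section does not report.

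This matters because conversion to diabetes is the sole basis for the 600 participants. A reader cannot tell what difference, over what period, the study is meant to detect. Nor can the reader tell whether the 90% power implied by beta = 0.1 holds under the test that will be used.

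**Working it through.** **Inputs.** From section 2.10: p1 = 0.10, p2 = 0.057, one-sided z = 1.645, z for power = 1.282. Allocation is 1:1 (section 2.5). The two-sided deviate for section 2.11 is 1.96. The study length is taken as 2.5 years (24 weeks plus 24 months; Table 1 ends at 30 months).

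**Step 1: the plan's figure from its own inputs.** With d = p1 − p2 = 0.043 and mean risk p̄ = 0.0785:

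- 2p̄(1 − p̄) = 0.14468, square root 0.38036
- p1(1 − p1) + p2(1 − p2) = 0.09 + 0.05375 = 0.14375, square root 0.37915
- n = (1.645 × 0.38036 + 1.282 × 0.37915)² / 0.043² = 1.1118² / 0.001849 = 668.5 per group

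Other forms give 666.1 (unpooled variance), 670.4 (pooled variance), 658.2 (arcsine) and 714.2 (continuity-corrected). None is near 299.94. The other rate pairs in the section do not return it either: 10% vs 1.5% gives 108 to 129, and 5.7% vs 1.5% gives 306 to 337.

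**Step 2: power at 300 per group if these are one-year risks.** Power = Φ[(d√n − z√(2p̄(1 − p̄))) / √(p1(1 − p1) + p2(1 − p2))].

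- One-sided: (0.043 × 17.3205 − 1.645 × 0.38036) / 0.37915 = 0.314, so 62.3%
- Two-sided: (0.7448 − 1.96 × 0.38036) / 0.37915 = −0.002, so 49.9%

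**Step 3: the same rates accumulated over a longer horizon.** Compounded risk is 1 − (1 − p)^t; over 30 months that is 1 − 0.9^2.5 = 23.2% and 1 − 0.943^2.5 = 13.6%. The simple versions multiply the rate by the years. The required n is at one-sided 0.05 and 90% power without continuity correction. The last column assumes 20% loss, a figure that is not in the article.

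| Horizon | Risks | n per group needed | One-sided power, 300 | Two-sided power, 300 | Two-sided power, 240 (assumed 20% loss) |
|---|---|---|---|---|---|
| 1 year | 10% vs 5.7% | 658–670 | 62% | 50% | 42% |
| 2 years, doubled | 20% vs 11.4% | 301–307 | 89.6% | 83% | 74% |
| 2 years, compounded | 19.0% vs 11.1% | 343–349 | 86% | 78% | 68% |
| 30 months, compounded | 23.2% vs 13.6% | 280–285 | 91% | 85% | 77% |
| 30 months, linear | 25% vs 14.25% | 230–234 | 95% | 91% | 84% |

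For 10% vs 5.7%, the standard two-proportion formulas come closest to 299.94 when the rates are doubled to two years. A continuity-corrected calculation on the 30-month compounded risks gives 303. No variant tried returns 299.94 exactly, so the origin of the figure remains an inference.

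**The case against.** The strongest reply is that annual rates are not whole-study risks. Incident diabetes is an end point of a study that measures glucose out to 30 months, so cumulative risk over 2 to 2.5 years is the natural quantity. On that basis 300 per group has about 86% to 95% one-sided power, a range that contains 90%. Doubling to two years needs 301 to 307, within about 2.5% of the printed figure. A journal article may also leave the derivation to the full protocol.

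Most of this stands. A reader might infer from step 1 that the study needs more than twice its sample, or that it has 62% power instead of 90%. The documents do not support either inference: both treat one year's risk as the risk over the whole study. Nor can it be said that a null result on the primary outcome would be uninformative. Section 2.6.2 names changes in glucose and HbA1c as primary, and this calculation does not address power for those.

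Three things are not answered:

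- An article may omit a formula, but this one prints inputs and a result that disagree.
- Any multi-year reading assumes that the 5.7% rate lasts for two years after a 24-week treatment. Section 2.10 neither states nor justifies that.
- Under the two-sided test, 90% is reached only if the rates are added linearly over 30 months with no loss.

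The mismatch between one-sided sizing and two-sided testing, and the absence of a loss allowance, are issues in their own right. They enter here only because a restated power must be the power of the analysis to be done. Section 3 speaks of compliance and gives no loss rate, so the 20% is purely illustrative.

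**Conclusion.** The point holds as an error in the stated derivation. The printed inputs need about 658 to 670 per group, and 299.94 is not obtained from them. The likeliest cause is an unstated horizon, probably two years with the annual rates doubled.

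The power of 600 participants for conversion to diabetes depends on that horizon. One-sided, it is 62% for one-year risks and about 86% to 95% over 2 to 2.5 years. Two-sided, it is 50% at one year, 78% to 83% at two years and 85% at 30 months compounded. The multi-year values rest on two assumptions: the annual rates persist after treatment ends, and follow-up is complete. All power values are normal approximations for comparing two proportions. The 90% claim is therefore unsupported as written, but the sample has not been shown to be inadequate.

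**What to change.** Keep the total at 600 and rewrite section 2.10 so that it gives:

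1. the time horizon and the cumulative risk in each group;
2. the formula;
3. the power of 300 per group under the two-sided test of section 2.11, with complete follow-up and with an assumed loss;
4. an explicit statement that the annual rates are assumed to persist after the 24-week treatment period.

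One possible wording: over 30 months, with annual rates compounded to 23.2% vs 13.6% and assumed to persist after treatment, 300 per group gives 85% power at two-sided 0.05 with complete follow-up, and 77% if 20% are lost (assumed).

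If one-year risks are what is meant, state 62% one-sided and 50% two-sided. In either case remove the 90% claim unless the inputs then printed support it.

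The cost is a change of wording and, on most readings, a lower stated power. No further participants are needed.
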